#### Post-therapy assessment

During and following the intervention phase, participants undergo the same assessments (MoCA and FMA) as performed in the pre-therapy stage. These assessments will occur immediately after therapy, at four weeks mid-intervention, after completion of six weeks, and again at six months post-intervention to evaluate both short- and long-term effects. This sequence will enable to monitor any improvements, non-improvement, or declines in cognitive and motor functions over time.

#### Dosage comparison

In both the rTMS and tDCS groups, the intervention is applied at three different dosage levels to identify the most effective parameters for enhancing cognitive and motor outcomes. The response to each dosage is compared across groups, considering factors such as accuracy of motor function improvement, cognitive gains, and patient tolerance. This comparative approach aims to optimize the therapeutic dose, balancing efficacy with safety. If a lower frequency or amplitude is found to be equally effective to a higher frequency or amplitude, then the study will conclude by recommending a lower frequency or amplitude.

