## Abstract

This randomized controlled trial investigates the optimal dosing for post-stroke rehabilitation using repetitive transcranial magnetic stimulation (rTMS) and transcranial direct current stimulation (tDCS). Previous studies demonstrated improvements in cognitive and motor functions with specific intensities of rTMS and tDCS, but this trial explores various frequencies and currents to optimize therapeutic outcomes. A total of 128 post-stroke patients (within 1–6 months of stroke) with paraplegia or hemiplegia are recruited. Patients are divided into four groups for both rTMS (n = 49) and tDCS (n = 49): three groups with different stimulation intensities (1 Hz, 5 Hz, 10 Hz for rTMS; 0.5 mA, 1 mA, 2 mA for tDCS) and a sham control group. Along with this, there is a standard therapy group (n = 30) as control. Participants receive 20 min sessions, five days a week, over six weeks. Cognitive and motor assessments are conducted at 4 weeks, 6 weeks, and 6 months to measure short-term and sustained effects.•Hemodynamically stable post-stroke patients randomized in four groups in rTMS and tDCS each and their baseline cognitive and motor function assessed•Application of the two types of therapy for 6 weeks•Checking improvement of cognitive and motor function and compare the improvement among subgroups of recipient of various frequencies and currents

Hemodynamically stable post-stroke patients randomized in four groups in rTMS and tDCS each and their baseline cognitive and motor function assessed

Application of the two types of therapy for 6 weeks

Checking improvement of cognitive and motor function and compare the improvement among subgroups of recipient of various frequencies and currents

Specifications table

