**Fig. 1 fig0001:**
[figure not shown]
Patient randomization and allocation.

To achieve this, researchers employ a randomized selection process using identically folded chits marked with group codes (e.g., a chit A-iii will allocate the patient to active rTMS of 10 Hz). Each participant selects a chit from a bowl, ensuring an unbiased distribution across groups and avoiding selection bias.

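### The rule recommending the lower setting does not define equal effectiveness, and arms of about 12 patients cannot establish it

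*Protocol article*

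**What the plan says.** The Dosage comparison section of the protocol article states how the trial will end: if a lower frequency or current is "found to be equally effective to a higher frequency or amplitude, then the study will conclude by recommending a lower frequency or amplitude". The doses are compared "considering factors such as accuracy of motor function improvement, cognitive gains, and patient tolerance". None of these factors is ranked as deciding, and no test, confidence level or margin is attached.

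The Abstract gives the numbers: "Patients are divided into four groups for both rTMS (n = 49) and tDCS (n = 49"), made up of "three groups with different stimulation intensities (1 Hz, 5 Hz, 10 Hz for rTMS; 0.5 mA, 1 mA, 2 mA for tDCS) and a sham" group, and in addition "there is a standard therapy group (n = 30) as control". The text under Fig. 1 describes allocation by drawing folded chits from a bowl and states no ratio within a modality. The Post-therapy assessment section applies two scales, MoCA and FMA, at several times up to six months after the intervention.

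**The concern.** Dose optimisation is the stated purpose of the trial, and this sentence turns its data into a recommendation. A claim that two settings are equally effective is a positive claim. It needs evidence that any advantage of the higher setting is smaller than some amount fixed in advance. Without that amount, a failure to find a difference can be reported as equality, and in small arms such failures are common even when the settings do differ.

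Because outcome, time point and criterion are all open, what counts as equal could also be settled after the data are seen. At stake is a recommendation that may reflect imprecision, not similarity of effect.

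**Working it through.** **Inputs from the protocol article.** Total 128 = 49 + 49 + 30, which agrees with the Abstract. Each modality has four groups, so 49/4 = 12.25 patients per arm; n = 12 is used below. The near-equal split is an assumption, since Fig. 1 is not shown.

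**Inputs assumed, because the article gives none.** Two-sided alpha 0.05, no dropout, and differences and margins in SD units. The article states no power, effect size, SD or margin, so there is no design calculation to reproduce.

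**Precision.** The standard error of a difference between two arms is √(2/12) = 0.408 SD. With t(22 df, 0.975) = 2.074, the 95% CI half-width is 2.074 × 0.408 = 0.85 SD. An observed difference of exactly zero would therefore still be compatible with a true advantage of about 0.85 SD either way.

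**Reading 1: a non-significant difference counts as equal.** Power comes from the noncentral t distribution with 22 df and non-centrality d/0.408. The lower setting of a pair is kept with probability 1 − power.

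| True advantage of higher setting (d) | Non-centrality | Power | Lower setting kept |
|---|---|---|---|
| 0.5 SD | 1.22 | 22% | 78% |
| 0.8 SD | 1.96 | 47% | 53% |
| 1.0 SD | 2.45 | 65% | 35% |
| 1.2 SD | 2.94 | 80% | 20% |

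The 50% point is at d = 0.84 SD. A Bonferroni correction for the three dose pairs in a modality (alpha 0.05/3) cuts power to 11% at 0.5 SD and 29% at 0.8 SD.

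*Baseline adjustment.* If baseline and outcome correlate at 0.7 (assumed), the residual SD is √(1 − 0.49) = 0.714. Power becomes 37% at 0.5 SD, 75% at 0.8 SD and 91% at 1.0 SD, so the lower setting is kept in about 63%, 25% and 9% of trials.

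*Three doses.* A simulation of 40,000 trials per scenario kept the lowest setting unless a higher one was significantly better (unadjusted t-tests). With true means rising evenly, the lowest was kept in about 74% of trials at 0/0.25/0.5 SD, 50% at 0/0.4/0.8, 33% at 0/0.5/1.0 and 19% at 0/0.6/1.2.

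**Reading 2: equality must be shown against a margin.** Take a true difference of zero and require the upper limit of the two-sided 95% CI (one-sided 0.025) to lie below the margin m. By the noncentral t with non-centrality m/0.408, non-inferiority is shown in 22% of trials at m = 0.5 SD, 47% at 0.8 SD and 65% at 1.0 SD. A chance of 80% needs m of about 1.2 SD. With the same baseline adjustment, the 22% becomes about 37%.

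The arm size for 80% power is n = 2 × ((1.96 + 0.842)/m)² (normal approximation): 63 at 0.5 SD, 25 at 0.8 SD and 16 at 1.0 SD, against about 12 planned.

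**Reading 3: observed means are compared.** Exactly equal means will almost never occur, so the rule would hardly ever apply. If the best observed mean simply wins, the lowest setting ranks first in only about 7% of simulated trials at 0/0.25/0.5 SD.

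**The case against.** A reader might infer that the rule will usually recommend the lowest dose even when a higher one is clearly better. The article does not support that, for four reasons.

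- It never says that a non-significant difference counts as equal. The bias toward the lower setting belongs to Reading 1 alone. Under a margin, small arms work the other way, because equality can rarely be shown.
- Even under Reading 1, the lower of a pair is kept more often than not only when the true difference is below about 0.84 SD. At 1.0 SD the higher setting is detected in most trials.
- The unadjusted t-test is pessimistic. The Patient allocation section collects baseline MoCA and FMA to support the later comparison. At a correlation of 0.7, the 50% point falls to 0.84 × 0.714 = 0.60 SD.
- A steadily rising dose-response is doubtful for rTMS. The Background cites low frequency as the more effective for motor recovery. The Therapy text and Table 1 both put 1 Hz on a different side from 5 and 10 Hz, though they label the sides differently. The three-dose simulation is therefore illustrative only.

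It can also be said that margin and test belong in a full protocol or analysis plan, which is not shown. That is fair for a detail left out. Here, though, the article states the conclusion it will draw and the condition for it, and a margin held elsewhere would not enlarge the arms. The objections limit how the point is put; they do not make the rule usable.

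**Conclusion.** The point holds in conditional form. The trigger for the recommendation is undefined, and about 12 patients per arm cannot support a conclusion of equality, since the 95% CI spans ±0.85 SD. If non-significance is read as equality, a setting inferior by 0.5 SD is kept in about 78% of trials unadjusted, or about 63% with a baseline correlation of 0.7. If a 0.5 SD margin is used, truly equal settings pass in only about 22% of trials, or about 37% with that adjustment.

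These sizes rest on the assumed alpha, the near-equal split, no dropout and illustrative effect sizes and margins. That the rule is undefined rests on none of them.

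**What to change.** Name one deciding outcome and time point for the dose comparison, for example FMA at six weeks adjusted for baseline; the article designates no primary outcome among its two scales and several assessments. State a margin in points of that scale before unblinding. Then replace the rule with wording such as:

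*A lower setting will be concluded to be as effective as a higher one only if the two-sided 95% confidence interval for higher minus lower on the deciding outcome lies below the pre-stated margin. Otherwise the comparison will be reported as inconclusive, with estimates and confidence intervals for each setting. Dose selection is exploratory.*

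The change is one of wording, and it favours no particular dose. The cost is that the trial will often report an inconclusive comparison instead of a recommendation. Avoiding that would take far larger arms (63 each at a 0.5 SD margin, unadjusted).

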## Limitations

This protocol has some limitations beyond our capability to adjust. Patient responses to non-invasive brain stimulation (NIBS) techniques like rTMS and tDCS can vary widely due to differences in brain structure, stroke severity, and neural plasticity. This variability can make it difficult to generalize optimal parameters across a diverse population. Additionally, the strict inclusion and exclusion criteria used to select participants may limit generalizability, as individuals with more severe impairments or certain comorbidities might respond differently to the treatment. Furthermore, the study uses fixed dosing parameters (frequencies and intensities) for rTMS and tDCS, which might not be optimal for each patient. Although necessary for research consistency, the lack of individualized dosing could limit the intervention's overall efficacy. Additionally, while the six-week intervention duration and single six-month follow-up provide insights into short- and medium-term effects, a longer follow-up period would be needed to determine lasting benefits. However, we are limited by the logistics of the study.

## Data Availability

No data was used for the research described in the article.
